#### Inpatient counseling and treatment plan—OPT IN

For patients in OPT IN, staff will screen for willingness to stay having quit after leaving the hospital. Patients who are willing to quit will be offered similar counseling, treatment planning, and medications as patients in OPT OUT, including a pamphlet with tips on quitting. However, instead of proactively providing these services, staff will ask patients if they would like each element of the treatment plan—post-discharge counseling and/or post-discharge prescription for medication. Patients will only receive the elements of care to which they opt in.

Patients in OPT IN who are not willing to quit will receive brief intervention, in accordance with current treatment guidelines. This consists of a four-page pamphlet with resources for quitting and a brief counseling session that addresses the “5 Rs” of motivational counseling (*Relevance, Risks, Rewards, Roadblocks, Repetition*) [3].

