#### Month-1 call for service data collection and informed consent

In accordance with standard procedures in the existing UKanQuit treatment program [20, 24], study staff will call all patients at 1 month post enrollment to assess outcomes including smoking status, quit attempts, counseling utilization, medication use, and other factors related to quitting (see Table 3, Core study measures). At the close of the call, study staff will verbally debrief patients on their inclusion in the trial and invite them to participate in the study. Study staff will collect additional data related to study outcomes.

**Table 3 Tab3:** Core study measures

	Baseline	Month 1	Month 6
Outcomes			
7-day point-prevalence abstinence		✓	✓
Biochemical quit verification		✓	✓
Number of quit attempts since enrollment		✓	✓
Post-discharge counseling adherence/other support		✓	✓
Medication use/adherence		✓	✓
Sociodemographics/mediators/moderators			
Demographics: age, gender, race	✓		
Length of hospital stay (for index visit)	✓		
Reason for hospitalization (index visit)	✓		
Readiness to quit, craving/withdrawal	✓	✓	
Number of cigarettes per day (cpd); time to first cigarette	✓	✓	
Motivation/confidence quit/stay having quit	✓	✓	
Default constructs (perceived status quo, etc.)		✓	
Rehospitalization		✓	✓
Cost measures			
Counseling		✓	✓
Nicotine Replacement Therapy (NRT) (calculated from patient self-reported use)		✓	✓

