#### Projected quit rates

As defined in the 2012 Cochrane review of smoking cessation in hospitalized patients [35], across both study arms, smokers who receive post-discharge support and medications will receive level-4 intensity treatment and smokers who receive only inpatient brief counseling will receive level-1 intensity treatment. Pooled quit rates are 10% for level-1 intensity studies and 29% for level-4 intensity studies [35]. Based on EQUIP and other trials, we estimate that 30% of OPT-IN participants will be ready to quit and receive services [36, 37]. For OPT OUT, based on the Inter99 trial and our pilot study on proactive quitline counseling we estimate that 80% of patients will accept services [38, 39]. We calculate the proposed quit rates within each condition using the following formula:$$ \left[\left(\mathit{\mathsf{prop}}.\mathit{\mathsf{receivingservices}}\times \mathit{\mathsf{level}}\ \mathit{\mathsf{4}}\ \mathit{\mathsf{quitrates}}\right)+\left(\mathit{\mathsf{prop}}.\mathit{\mathsf{not}}\ \mathit{\mathsf{receivingservices}}\times \mathit{\mathsf{level}}\ \mathit{\mathsf{1}}\ \mathit{\mathsf{quitrates}}\right)\right]. $$

We estimate the quit rate to be 15.7% in the OPT-IN group: [(.30 × .29) + (.70 × .10)] = .157. We estimate the quit rate to be 25.2% in the OPT-OUT group: [(.80 × .29) + (.20 × .10)] = .252.

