Hypothesis 1: compared to OPT IN, significantly more patients in OPT OUT will participate in counseling, use cessation medications, and be abstinent from smoking	Abstinence: treatment condition and 1-month 7-day point-prevalence abstinence	2-sample binomial test
	Counseling: treatment condition and total counseling time by 1 month	2-sample lognormal test
	Medication: treatment condition and number of days of medication use	2-sample Poisson test
Hypothesis 2: significantly more smokers in OPT OUT will be abstinent from smoking, and mediation analyses will partially or fully explain the effects	Treatment condition and 6-month and • 7-day point-prevalence abstinence • Default variables • Counseling/medication use	Bayesian structural equation modeling with a logistic outcome
Hypothesis 3: OPT OUT will be more costly but also more effective than OPT IN	Treatment condition and 1-month abstinence • Variable costs	Incremental cost/quit

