#### Analyses by aim

The main analyses for each aim are outlined below (Table 5).

Aim 1. Hypothesis 1: among patients consented into the trial, significantly more patients in OPT OUT will participate in counseling, use cessation medications, and be abstinent from smoking at 1 month post randomization compared to OPT IN. These analyses will involve two-sample tests.

Aim 2. Hypothesis 2: significantly more smokers in OPT OUT will be abstinent from smoking, and mediation analyses will find that counseling participation, medication use, and default-theory-based variables will partially or fully explain the effect of OPT OUT on cessation at 6 months post randomization. After identifying a structural equation model that adequately fits the data for the hypothesized associations between the intervention and 6-month outcome, i.e., that Comparative Fit Index (CFI) > .9 and Root Mean Square Error of Approximation (RMSEA) < .8, we will examine mediation using approaches based on the work of MacKinnon et al. [49], Brown [50], and Shrout and Bolger [51]. Our theoretical model (Fig. 1, Significance) will guide our analysis.

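### The variables stated for the Aim 2 mediation model omit baseline readiness to quit, which decides who receives services in OPT IN but not in OPT OUT, so the indirect effect through services can be biased upward

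*Protocol article*

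**What the plan says.** Under Analyses by aim, Hypothesis 2 holds that counseling participation, medication use and default-theory variables "will partially or fully explain the effect of OPT OUT on cessation at 6 months post randomization". The Hypothesis 2 row of Table 5 names a Bayesian structural equation model with a logistic outcome. Its variables are treatment condition, 6-month abstinence, default variables and "Counseling/medication use". Study procedures describes the same chain in words: perceptions, then counseling and medication, then quitting. The section on population drift lists factors for adjustment if the sample becomes unbalanced: cigarettes per day, time to first cigarette, sex, age and income. Readiness is in none of these places.

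The two arms reach services by different routes. In OPT IN, "staff will screen for willingness to stay having quit after leaving the hospital", and "Patients in OPT IN who are not willing to quit will receive brief intervention, in accordance with current treatment guidelines". In OPT OUT, every patient gets all elements unless they refuse. Projected quit rates treats readiness and service receipt as one thing in OPT IN: "we estimate that 30% of OPT-IN participants will be ready to quit and receive services". For OPT OUT, "we estimate that 80% of patients will accept services".

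Readiness is recorded at baseline (Eligibility and baseline assessment). Table 3 has a row "Readiness to quit, craving/withdrawal", ticked at baseline and month 1, under a heading that covers sociodemographics, mediators and moderators. Motivation/confidence, cigarettes per day and time to first cigarette are ticked at the same visits.

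**The concern.** A mediated effect is built from two paths. Randomization protects the first, from arm to service use. It does not protect the second, from service use to quitting given arm. In OPT IN the design makes service users largely the ready smokers and non-users largely the unready. If ready smokers quit more often regardless of treatment, service use will be associated with quitting within arm even when services do nothing. The very large first path (30% v 80%) then carries that association into a non-zero indirect effect and pushes the direct effect down. The fit criteria (CFI, RMSEA) do not detect an omitted confounder.

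This matters because the mediation analysis is meant to show why changing the default did or did not work, and the Discussion sets the trial against the rival explanation that smokers lack motivation. A model without readiness cannot separate effective services from ready smokers who both take services and quit.

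**Working it through.** **The plan's own figures.** Projected quit rates states: "Pooled quit rates are 10% for level-1 intensity studies and 29% for level-4 intensity studies". Weighting by uptake:
- OPT IN: 0.30×0.29 + 0.70×0.10 = 0.157
- OPT OUT: 0.80×0.29 + 0.20×0.10 = 0.252

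Both match the article. It gives no error rate for the mediation analysis and no quit rate by readiness.

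**How the bias arises.** Assume that services have no effect, 30% of smokers are ready, ready smokers quit at 29% and others at 10% in both arms. These two rates are borrowed for illustration; the article gives them for treatment intensity, not readiness. Assume also a strict gate: OPT IN service users are exactly the ready, and the 80% served in OPT OUT include all the ready.
- OPT IN: users quit at 29%, non-users at 10%. Odds ratio = (0.29/0.71)/(0.10/0.90) = 3.68.
- OPT OUT: 0.30/0.80 = 37.5% of users are ready, so users quit at 0.375×0.29 + 0.625×0.10 = 17.1%; non-users quit at 10%. Odds ratio = (0.171/0.829)/(0.10/0.90) = 1.86.
- Arm totals: OPT IN 0.30×0.29 + 0.70×0.10 = 15.7%; OPT OUT 0.80×0.17125 + 0.20×0.10 = 15.7%.

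Inert services thus show within-arm odds ratios of 3.68 and 1.86 with no arm difference at all. OPT IN comes out at the projected 15.7% whether services or readiness do the work.

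**How often this is declared mediation.** Simulation, 1500 trials per setting (Monte Carlo error up to 1.3 points), services inert:
- Sizes: N=625 (238 OPT IN, 387 OPT OUT, the article's average in the expected scenario) and N=1000 (500 per arm).
- Model: logistic regression of quitting on arm and binary service use, without and with readiness.
- Declaration: z > 1.96 for service use; the arm-to-services path is so strong that it is effectively always significant.
- Leaky gate: 70% of ready and 12.9% of unready served in OPT IN; 95% and 73.6% in OPT OUT. This keeps overall uptake at 30% and 80%.
- The last two columns add a 9.5-point direct effect of OPT OUT that bypasses services (0.252 − 0.157) and also require a significant total effect.

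Cells are percent of trials, N=625 / N=1000.

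| Ready v other quit rate; gate | No arm effect, readiness omitted | No arm effect, readiness added | Direct effect and total required, omitted | Same, added |
|---|---|---|---|---|
| 29 v 10; strict | 95 / 100 | 2 / 3 | 73 / 97 | 5 / 8 |
| 29 v 10; OPT OUT acceptance unrelated to readiness | 67 / 97 | 2 / 3 | 47 / 92 | 4 / 9 |
| 29 v 10; leaky | 61 / 89 | 3 / 2 | 42 / 77 | 3 / 5 |
| 22 v 13; strict | 41 / 70 | 3 / 3 | 26 / 60 | 3 / 4 |
| 22 v 13; leaky | 19 / 32 | 2 / 4 | 13 / 27 | 2 / 3 |
| 15 v 10; strict | 20 / 37 | 3 / 3 | 13 / 26 | 3 / 4 |
| 15 v 10; leaky | 10 / 16 | 2 / 2 | 7 / 13 | 2 / 3 |

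With no arm effect and a significant total effect required, false declarations are 0–3% in every row. In the first row, with no arm effect, the direct path is falsely negative in 45% / 74%. If readiness does not predict quitting, or does not gate services, the rate is about 2–3%.

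Adjustment works this well because readiness is the only confounder and is measured without error. With readiness wrong in 10% of patients (strict gate, 29 v 10), the false rate with adjustment is 37% / 68%. Part of the residual excess in the last column comes from fitting additive effects on the logit scale.

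**The case against.** The strongest reply is that the full model may well include readiness. Analyses by aim only outlines the main analyses, Fig. 1 is said to guide the model and is not shown, Table 5 gives one row per hypothesis, and Accounting for missing data refers to covariates it does not name. Table 3 groups readiness with mediators and moderators. This stands in part: the article does not prove that the final model omits readiness. But wherever the article states the variables, or lists factors for adjustment, readiness is absent, and the Table 3 heading also covers age and length of stay, so it places nothing in the model.

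A reader might infer that the plan will declare mediation in nearly every trial even if services are useless. The documents do not support that. It takes treatment-intensity quit rates read as readiness quit rates, a perfect gate, full acceptance by ready OPT OUT patients, and no requirement of a total effect. Hypothesis 2 as worded also expects more abstinence in OPT OUT, and requiring that holds the false rate to 0–3% when OPT OUT does nothing. That protection fails when OPT OUT works by another route. Study procedures, moreover, foresees using mediation to explain a default that did not work.

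Two further points stand. Inert services are remote from the article's premise that treatment doubles quit rates, so the likelier harm is an inflated mediated share rather than mediation from nothing. And the planned mediators are total counseling time, days of medication use and perceptions, not one binary variable, so the simulation shows direction and rough scale only.

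**Conclusion.** The concern holds in conditional form. The stated variable set omits a baseline factor that the design itself ties to service use in one arm, and the services-to-quitting path is not randomized. If ready smokers quit more often whatever they receive, the indirect effect through services is biased upward and the direct effect downward.

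The size depends on figures the article does not give. With inert services and no arm effect, false declaration ranges from roughly 10% to 100% across readiness contrasts of 5 to 19 points and strict to leaky gates. When a total effect is also required and a 9.5-point effect bypasses services, a strict gate with contrasts of 9 to 19 points gives about 25–95%; the weakest settings give about 7–13%. These figures rest on a binary mediator, fixed arm sizes and a frequentist stand-in for the Bayesian model. The primary 1-month abstinence comparison is unaffected. The change should be made, because it concerns the reading of Aim 2 and needs no new data.

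**What to change.** In Analyses by aim (Hypothesis 2) and the matching row of Table 5:
- Name baseline readiness to quit, motivation/confidence, cigarettes per day and time to first cigarette as covariates in both the mediator and the outcome equations.
- Prespecify a sensitivity analysis for residual mediator–outcome confounding, since readiness is self-reported and will not be the only confounder.
- State that the indirect effect, unlike the arm comparison, is not protected by randomization.

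An arm-by-service interaction need not be required. Under a strict gate, service use nearly equals readiness in OPT IN, so the service effect in that arm could hardly be separated from readiness.

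The cost is a few lines of text, a slightly larger model and a somewhat wider interval for the indirect effect. All the covariates are already collected at baseline.

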#### Power, sample size, and trial duration

In accordance with guidelines for adaptive design power analyses [34], we used simulated data to determine the power, sample size, and anticipated duration of the study. We created virtual responses for our “expected” quit rates, another for “small but unlikely” quit rates, and a third for “no differences” in quit rates. We performed three sets of trial simulations (Table 4). Each set involved many trial simulations that identified power (the probability of success) in two scenarios—one for early success (i.e., being able to stop randomization early) and one for late success (i.e., upon enrolling all 1000 patients). While two of these combinations are very unlikely to occur, we included all scenarios. First, under the “expected” quit rates, we estimated (identified) that 92% of the simulated trials had early success, 3% late success, and only 5% had incomplete results. Thus, this scenario had 95% power. The average sample size of this trial scenario was 625 patients with more than half (387) in the better OPT-OUT arm. The average length of these simulated trials was 98 weeks. Second, if there are “small but unlikely” quit rates, we identified that 30% of the simulated trials had early success, 5% had late success, and 65% had incomplete results. This trial scenario had 35% power and the sample size of this trial scenario was on average 903 with more than half (530) in the better OPT-OUT arm. The average length of this trial scenario was 142 weeks. Third, we examined the scenario that serves as our null hypothesis. In this scenario there are no differences in quit rates among the arms. The extent to which this scenario is “successful” reflects our Type-I error rate. For this scenario, we identified that 4% of the simulated trials had early success, 1% late success. This trial scenario produced an appropriate expected Type-I error (*α* = .05). The sample size of this scenario on average was 986 patients, with about half (495) in the OPT-OUT arm. The average length of the trials under this scenario was 155 weeks—approximately 3 years of recruitment. Hence, our maximal sample size of 1000, in 3 years of recruitment, provides ample time and participants to identify project outcomes under all three scenarios.

**Table 5 Tab5:** Study hypotheses, measures, and analytic strategy

Purpose	Variables	Analytic strategy

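### The CFI and RMSEA condition set before the mediation analysis does not match the Bayesian logistic model named for Hypothesis 2, and is not operational as written

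*Protocol article*

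**What the plan says.** Table 5 of the protocol article (printed in the section on power, sample size and trial duration) gives the analytic strategy for Hypothesis 2 as "Bayesian structural equation modeling with a logistic outcome". The outcome is binary: the hypothesis is that counseling, medication use and the default variables "will partially or fully explain the effect of OPT OUT on cessation at 6 months post randomization".

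The Analyses by aim section puts a condition ahead of the mediation step. It begins "After identifying a structural equation model that adequately fits the data for the hypothesized associations between the intervention and 6-month outcome" and defines adequate fit as "Comparative Fit Index (CFI) > .9 and Root Mean Square Error of Approximation (RMSEA) < .8". Only then does it continue: "we will examine mediation using approaches based on the work of" the cited methodological authors. The paragraph closes by saying that the theoretical model in Figure 1 will guide the analysis.

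The article names no fit measure belonging to a Bayesian model and no auxiliary estimator that would supply CFI or RMSEA. It does not say what follows if the cut-offs are missed.

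**The concern.** The rule that admits a model to mediation testing is written for one kind of model, and the analysis is planned with another. CFI and RMSEA compare a fitted mean and covariance structure with an unrestricted one through a chi-square. A full-likelihood Bayesian fit with a logit-link binary outcome does not report that chi-square, so an analyst who follows Table 5 reaches the condition without the quantities needed to apply it.

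Two things are at stake. First, the analyst has to add a step that the plan does not describe, and two analysts could add different steps and admit different models. Second, the condition is worded as a model to be identified, with no limit on how it is reached. If paths are altered until the fit is acceptable, and indirect effects are then estimated from the same data, the reported uncertainty leaves out the selection. Mediation is one of the article's stated purposes, so the route to that result should be fixed before outcome data are analysed.

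**Working it through.** The plan gives no figure to reproduce here. The check sets the two statements side by side and then asks what the printed RMSEA limit allows.

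**1. What the indices need.**
- RMSEA = sqrt( max(χ² − df, 0) / (df × (N − 1)) )
- CFI = 1 − max(χ²_M − df_M, 0) / max(χ²_B − df_B, χ²_M − df_M, 0), where M is the fitted model and B the baseline model.

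Both require a model chi-square against an unrestricted mean and covariance structure, and CFI also requires a baseline chi-square.

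**2. What the named model gives.** Markov chain Monte Carlo fitting of a model with a logit link for a binary outcome gives posterior distributions of the parameters. The chi-square above is not part of its standard output.

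**3. Would a substitute fit carry over?** A limited-information probit fit, or a linear fit of the same paths, would yield the indices, but under a different link or different distributional assumptions. Under Hypothesis 1, Table 5 treats counseling time as lognormal and medication days as Poisson. If the mediators keep those distributions in the Hypothesis 2 model (an assumption, since the article does not say), the distance from a covariance-structure fit grows. The section on missing data plans Bayesian posterior predictive handling of missing covariates, which a substitute estimator might not share. A pass or fail from the substitute need not hold for the named model.

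**4. What the printed RMSEA limit allows.** Setting RMSEA equal to the limit c and solving gives χ²/df = 1 + c² × (N − 1). N comes from the section on power: "our maximal sample size of 1000", and for the expected scenario "The average sample size of this trial scenario was 625 patients".

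| N | c = .8 (as printed) | c = .08 (for comparison) |
|---|---|---|
| 1000 | 1 + 0.64 × 999 = 640.4 | 1 + 0.0064 × 999 = 7.4 |
| 625 | 1 + 0.64 × 624 = 400.4 | 1 + 0.0064 × 624 = 5.0 |

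**5. Could a plainly wrong model pass at .8?** Take p variables with every pairwise correlation equal to r, and fit a model with no associations at all. Its population RMSEA is sqrt(F/df), with F = −[(p − 1) ln(1 − r) + ln(1 + (p − 1) r)] and df = p(p − 1)/2. The values of p and r are assumptions chosen to show the range.

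| p | r = .5 | r = .7 | r = .8 | r = .9 |
|---|---|---|---|---|
| 4 | 0.440 | 0.643 | 0.775 | 0.966 |
| 6 | 0.384 | 0.549 | 0.655 | 0.809 |
| 8 | 0.346 | 0.487 | 0.579 | 0.710 |

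For p = 6 and r = .8: F = −[5 ln 0.2 + ln 5] = 6.438, df = 15, and sqrt(6.438/15) = 0.655. A model that denies every association passes a limit of .8 in all three rows up to r = .8. Even where RMSEA can be computed, only the CFI half would screen models.

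**The case against.** The strongest reply is that the mismatch can be bridged. Bayesian analogues of CFI and RMSEA can be computed from posterior discrepancies, or the same path model can be fitted with a limited-information estimator for the fit check alone. The text asks only for a structural equation model that fits; it does not say that the indices must come from the Bayesian run. The choice of estimator for a secondary analysis can also be left to a full analysis plan that is not shown. This stands to the extent that a reader might infer that the indices are undefined or that the condition can never be evaluated, and the documents do not support that. What remains is that the article fixes a rule and a model that do not fit each other, which is more than an omitted detail.

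Three further inferences are tempting and go too far:
- **An open search for paths is planned.** The sentence refers to hypothesized associations, the theoretical model is to guide the work, and the Study procedures section states the causal chain in advance. The wording permits re-specification but does not announce it, so indirect-effect intervals would be too narrow only if re-specification happens.
- **The model is saturated, so the indices are perfect by construction.** With zero degrees of freedom CFI is 1 and RMSEA is 0 for any data, but Figure 1 is not shown and nothing in the text says that all paths are free.
- **All of Hypothesis 2 depends on the condition.** It is placed before the mediation step, and the 6-month abstinence comparison between arms need not wait for it.

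**Conclusion.** The point holds as a mismatch between a stated criterion and a stated model. As written, the CFI and RMSEA condition is not operational for the model in Table 5. It could be applied only by adding something unplanned, and a verdict from a second model need not apply to the first. The wording also leaves room for data-driven re-specification before indirect effects are tested.

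The printed RMSEA limit is a separate fault in the same sentence. It tolerates chi-square/df of about 640 at N = 1000 and 400 at N = 625. It is probably a decimal slip for .08, but that is an inference. Correcting it alone would not remove the mismatch.

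The reach is limited to the mediation part of Hypothesis 2. No stated trial figure changes, and the primary 1-month analysis, the adaptive allocation, the stopping rule and the sample size are unaffected. The conclusion assumes that Table 5 means a full-likelihood Bayesian fit with a logit link. It is worth settling before outcome data are analysed.

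**What to change.** 1. Write the Figure 1 paths into the plan as the pre-specified mediation model.
2. Replace the CFI and RMSEA condition with posterior predictive checks suited to the Bayesian logistic model: observed against predicted quit proportion by arm and by service use, and observed against predicted mediator distributions. Report them beside the mediation result, so that a reader can weigh the indirect effects against the fit. If fit is poor, say so and qualify the interpretation.
3. Label any re-specified model exploratory.
4. If the authors prefer to keep CFI and RMSEA, name the auxiliary estimator that yields them, say how its verdict bears on the Bayesian model, and correct the RMSEA limit.

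The cost is a few sentences of wording and standard posterior predictive output, with no new data. The downside is the loss of a single pass/fail index, so judging fit becomes a matter of reported evidence.

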#### Bayesian design

We will perform a prospective randomized comparative effectiveness *Bayesian adaptive design study* [34]. Our endpoint is the percentage of patients with verified cessation at 1 month (4 weeks) post randomization. We will perform our first planned interim analyses when we have endpoint data on 400 patients. The arm that appears to be performing the best will get more participants allocated to it in the subsequent randomization period. A new adaptive randomization structure will be updated every 13 weeks, using up-to-date outcome data, until the trial meets success or all 1000 subjects are consented. The main outcome analysis will use an ITT approach, with the denominator being all participants randomized to the study. Data from patients we are unable to reach at 1 month will be de-identified and included in data analyses.

For this study the primary endpoint is modeled:
*S*
_*QjT*_|*n*
_*jT*_ ~ Bino(*n*
_*jT*_
*,θ*
^*Q*^
_*j*_) quitting.

In addition, we provide “weakly informative” priors:logit(*θ*
^*Q*^
_*j*_) ~ N(0,100^2^).

Using the endpoint data and the prior probabilities, we then use Markov Chain Monte Carlo computations to obtain the Bayesian posterior distributions for the endpoint (i.e., quitting). We will stop randomizing into the comparative trial if the probability of a study arm having maximum utility is greater than 0.9925. The arm having the maximum quit rate is *M*
_*T*_ = max(*θ*
^*Q*^
_*1,*_
*θ*
^*Q*^
_*2*_). The stopping rule is mathematically *P*(*M*
_*T*_ > .9925). If a maximum arm is not identified after 500 patients, this procedure and accrual will continue until a maximum arm is identified or we enroll all 1000 patients. It is possible that we will reach the maximum utility criterion before 1000 patients are consented. Should this occur, we will stop the trial and begin outcome, cost, and mediation analyses in order to quickly disseminate findings.

After the maximum arm probability is evaluated, the next round of patients is randomized using a formula that favors the arm with the maximum quit rate, thus taking advantage of the information gained from our interim analyses. Using this formula, each arm is allocated for the next patients to be enrolled in the *j*
^th^ arm proportional to:$$ {V^{\ast}}_j=\mathrm{sqrt}\Big(\Pr \left({M}_{jT}={\theta^Q}_1\Big)\mathrm{Var}\left({\theta^Q}_1\right)/\left({n}_{jT}+1\right)\right). $$

This type of allocation has more desirable properties than simply using Pr(*M*

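### The RMSEA limit of .8 for the Aim 2 mediation model is practically non-binding, so adequate fit rests on CFI > .9 alone; .08 was probably meant

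*Protocol article*

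**What the plan says.** Under Analyses by aim (Aim 2, Hypothesis 2), the protocol article makes the mediation analysis conditional on model fit. Mediation is examined "After identifying a structural equation model that adequately fits the data for the hypothesized associations between the intervention and 6-month outcome", and adequate fit is then given numbers: "Comparative Fit Index (CFI) > .9 and Root Mean Square Error of Approximation (RMSEA) < .8". Both conditions must hold.

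Table 5 names the method for this hypothesis as "Bayesian structural equation modeling with a logistic outcome" and gives no fit limits. The value .8 appears once, and nothing elsewhere in the article corrects it.

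**The concern.** RMSEA measures misfit per degree of freedom, so an upper limit on it is useful only if poorly fitting models can exceed it. A limit of .8 looks far too high for that. If so, the authors have named two criteria and only one of them works.

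The mediation analysis is where the trial explains why changing the default did or did not work, and the article lists psychological mediators among its expected contributions. Estimates of mediated effects depend on how the path model is specified. A fit rule fixed in print and set too loosely would let a model be described as meeting its prespecified criterion when one half of that criterion tested next to nothing.

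**Working it through.** The cut-off is a chosen threshold, so the plan has no figure to reproduce. The check is how strict the threshold is.

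**Inputs from the protocol article**
- Limits: RMSEA < .8 and CFI > .9 (Analyses by aim).
- N = 1000: "our maximal sample size of 1000, in 3 years of recruitment" (Power, sample size, and trial duration).
- N = 625, under the expected quit rates: "The average sample size of this trial scenario was 625 patients" (same section).
- N = 400, as a lower end: "first planned interim analyses when we have endpoint data on 400 patients" (Bayesian design).

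**Step 1: the misfit that the limit tolerates.** Classically, RMSEA = sqrt((chi-square/df − 1)/(N − 1)). A limit c therefore allows chi-square/df up to 1 + c² × (N − 1).

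| N | limit .8 | limit .08 |
|---|---|---|
| 400 | 1 + .64 × 399 = 256.4 | 1 + .0064 × 399 = 3.6 |
| 625 | 1 + .64 × 624 = 400.4 | 1 + .0064 × 624 = 5.0 |
| 1000 | 1 + .64 × 999 = 640.4 | 1 + .0064 × 999 = 7.4 |

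**Step 2: can a model with no associations meet the limit?** For p variables that all share a correlation r, the independence model (no paths) has population RMSEA = sqrt(−ln det R / df). Here det R = (1 − r)^(p−1) × (1 + (p − 1)r) and df = p(p − 1)/2. This benchmark does not depend on N. The article does not give p or r, so these are assumptions.
- p = 6, r = .5: det R = .5^5 × 3.5 = .109; RMSEA = sqrt(2.213/15) = .38. It passes .8.
- p = 6, r = .8: det R = .2^5 × 5 = .0016; RMSEA = sqrt(6.438/15) = .66. It still passes.
- Under .8, the no-paths model fails only when the common correlation exceeds about .82 (p = 4), .90 (p = 6), .94 (p = 8) or .98 (p = 12).
- Under .08, it fails once the common correlation exceeds about .08 to .10 (p = 4 to 12).

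**Step 3: what CFI > .9 still does.** With T the fitted model and B the baseline (no-paths) model, CFI = 1 − (RMSEA_T² × df_T)/(RMSEA_B² × df_B). The no-paths model has CFI 0 and fails. For any other model, CFI > .9 caps the fitted RMSEA at sqrt(.1 × RMSEA_B² × df_B/df_T). Baseline RMSEA (.2 to .5) and df_B/df_T (1.5 to 10) are again assumed.
- Tightest corner: sqrt(.1 × .04 × 1.5) = .08.
- Middle case, baseline .4 and ratio 3: sqrt(.1 × .16 × 3) = .22.
- Loosest corner: sqrt(.1 × .25 × 10) = .50.

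For CFI = .9 to be compatible with an RMSEA as high as .8, the df ratio would have to be .64/(.1 × RMSEA_B²). That is 25.6 at baseline .5 and 160 at baseline .2, both outside the assumed range. Over that range CFI always binds first and the RMSEA limit adds nothing. A limit of .08 would be the tighter of the two almost everywhere.

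**The case against.** The strongest reply is that the rule has two parts joined by *and*. A reader might infer from the RMSEA figure that the whole fit gate is empty, or that a badly misspecified model would be reported as adequate. The article does not support either inference: a model must still reach CFI > .9, and Step 3 shows that this rejects the no-paths model and caps RMSEA below .8. Nor is it right that .8 could never reject anything, since Step 2 shows that it fails the no-paths model at very high correlations. These points stand, and they limit the finding to one half of the gate.

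Three further points also stand:
- The chi-square/df conversion belongs to classical likelihood-based fitting. Table 5 plans a Bayesian model with a logistic outcome, for which a classical model chi-square is not directly available. The ratios in Step 1 therefore show the scale of the limit; they are not values the analysis would produce.
- The figure .08 appears nowhere in the article. It is an inference from the size of the slip and from Step 2, where .08 separates models and .8 does not.
- The reach is small: one secondary analysis.

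None of this makes .8 a working limit. The article chose to state two numerical criteria, so the value is not a detail left to a fuller document.

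**Conclusion.** The point holds for the RMSEA half of the gate. As printed, RMSEA < .8 is practically non-binding: on the classical formula it allows chi-square/df of about 256, 400 and 640 at N = 400, 625 and 1000. Acceptance of the Aim 2 mediation model therefore rests on CFI > .9 alone. Over the assumed baseline RMSEA and df ratios, CFI alone leaves room for a fitted RMSEA of about .08 to .50, so models well above .08 can be declared adequate.

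Step 1 rests on the classical definition of RMSEA and on sample sizes in the article. Steps 2 and 3 also rest on assumed correlations, numbers of variables and df ratios, because the article does not specify the model to that level.

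The effect is confined to the mediation analysis under Hypothesis 2. The 1-month primary endpoint, the adaptive allocation and stopping rule, the sample size and the cost analysis are untouched. The correction is worth making, but it does not threaten the trial's main conclusion.

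**What to change.** Before the Aim 2 analysis begins:
1. Confirm the intended RMSEA limit and, if it is .08 as seems very probable, correct the criterion to RMSEA < .08.
2. Keep CFI > .9, with both conditions required.
3. State which version of CFI and RMSEA will be computed for the Bayesian structural equation model with a logistic outcome, and confirm that the limits are meant for that version. The article gives no basis for assuming that cut-offs carry over from the classical indices.

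The cost is one figure and one sentence. The change makes the rule stricter and needs no new data and no change to the design or sample size.
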